# Using brain functional magnetic resonance imaging to evaluate the effectiveness of acupuncture combined with mirror therapy on upper limb function in patients with cerebral ischemic stroke: a study protocol for a randomized, controlled trial

**DOI:** 10.1186/s13063-020-04955-2

**Published:** 2021-01-12

**Keywords:** Upper limb and hand motor dysfunction, Cerebral ischemia, Mirror therapy, Jin’s three-needle acupuncture, fMRI, Randomized controlled trial

## Abstract

**Background:**

Upper limb and hand motor dysfunction is one of the challenges in rehabilitation after cerebral ischemic stroke (CIS), and the clinical efficacy of rehabilitation needs to be improved. This study aims to combine Jin’s three-needle acupuncture (JTN) therapy with mirror therapy (MT) for hemiplegia after CIS, objectively evaluate the clinical effects and safety of JTN to treat upper limb dysfunction, and use functional magnetic resonance imaging (fMRI) of the brain to investigate the central mechanisms of the effects, which would provide a powerful evidence-based medical basis for further supporting the application of JTN combined with MT.

**Methods/design:**

This trial will be a single-blind, randomized controlled study. Patients who meet the study criteria will be recruited and randomly assigned to either the combined treatment group (JTN+MT) or the JTN group. Both interventions will be conducted for 6 days per week and last for 4 weeks. The primary outcome will be the effective rate based on the Fugl–Meyer Assessment for Upper Extremity (FMA-UE). Other outcome measures will include scores on the motor assessment scale (MAS), action research arm test (ARAT), activities of daily living (ADL) scale, and fMRI analyses. For safety evaluation, adverse events will be observed and recorded.

**Discussion:**

This study may help to identify the efficacy and safety of acupuncture combined with MT for upper limb dysfunction after CIS and explore the central mechanisms with brain fMRI.

**Trial registration:**

Chinese Clinical Trial Registry ChiCTR-IOR-17012174. Registered on 5 April 2017.

## Background

Cerebral ischemic stroke (CIS) accounts for 80% of 12.42 million stroke patients aged 40 or older in China in 2017 [1]. If not promptly and adequately diagnosed and treated, CIS patients will suffer serious damage to the nervous system, become handicapped, or even die because of infectious complications [2].

Upper limb motor impairment is a common sequelae after stroke and restricts function in muscle movement or mobility [3], manifested as coordination and execution problems of the arms, palms, and fingers that result in restrictions on daily activities such as eating, dressing, and bathing [4]. Eighty percent of patients experience acute paresis of the upper extremity after stroke, and about 37% of the patients still have problems such as decreased control of upper limbs and hand fine motor skills [5] 3 months after stroke onset. However, rehabilitation of CIS patients with upper limb motor impairment continues to be challenging. We propose combining the use of Western Medicine and Traditional Chinese Medicine and determining whether the combination therapy will provide improved outcomes.

Functional magnetic resonance imaging (fMRI) technique, a noninvasive imaging technique with exceptional spatial and temporal resolution, is frequently used to study brain functional connectivities [6] and can monitor the progress of cortical functional remolding in stroke patients [7–9]. Because it can accurately determine whether the brain function in the motor areas disappears or shifts and whether there is reconstruction of the brain functional areas around the lesion [10], the technique can guide clinical rehabilitation and prognosis of patients.

Acupuncture has been used as part of Traditional Chinese Medicine (TCM) therapy to treat stroke for thousands of years. Jin’s three-needle acupuncture (JTN) therapy is a popular acupuncture technique due to its simple and easy manipulation. First developed by Rui Jin, a professor of Guangzhou University of Chinese Medicine, it has been widely used in China to treat post-stroke hemiplegia in the past decades. Satisfactory and promising effects have been reported in clinical trials [11–13].

Mirror therapy (MT), also known as mirror visual feedback (MVF) therapy [14], is a treatment method based on visual illusion, visual feedback, and virtual reality combined with a rehabilitation training program [5]. Previous studies have shown that MT was significantly associated with immediate improvement of upper extremity motor function in stroke patients [6, 15, 16] and has gradually been accepted by clinical researchers as a new treatment for post-stroke limb rehabilitation [6, 17].

Therefore, we hypothesize that the clinical efficacy of CIS will be improved with the combination of acupuncture therapy and MT. Based on the modern image technique, we may also find out the central brain mechanisms which could provide a strong evidence-based medical basis for further popularizing the application of JTN+MT in the treatment on upper limb function in patients with cerebral ischemic stroke.

**Fig. 1 Fig1:**
[figure not shown]
Flowchart of the trial. W, week, JTN, Jin’s three-needle acupuncture, MT, mirror therapy, fMRI, functional magnetic resonance imaging

### Inclusion criteria

The inclusion criteria include the following: (1) corresponding to the diagnostic standards of CIS [18]; (2) corresponding to the diagnostic standards of stroke of TCM [19]; (3) diagnosed with CIS and confirmed by CT or MRI; (4) first-ever clinical CIS occurred ≥ 2 weeks and ≤ 6 months previously, the number of times ≤ 2; (5) aged between 40 and 75, male or female; (6) limb function in NDS [20] score ≥ 10; (7) stable vital sign and consciousness; (8) normal test result of kinesthetic and imagery questionnaire [21]; and (9) provided written informed consent to participate.

### Exclusion criteria [7]

The exclusion criteria include the following: (1) transient ischemic attack (TIA); (2) upper limb dysfunction caused by brain tumor, brain trauma, and other diseases; (3) craniotomy requirement or hematencephalon; (4) sever spastic deformation on upper limb; (5) pregnant and lactating women; and (6) severe complications of heart, liver, kidney, hematopoietic system, and endocrine system or with a severe mental illness that prevents them from cooperating with treatment, including addiction and substance use disorders, dissociative disorders, and schizophrenia.

### Study setting

The treatment will be conducted at the rehabilitation department of Shenzhen Hospital of Guangzhou University of Traditional Chinese Medicine (Futian). The study will enroll 60 individuals in total, with 30 individuals in each group. Patients who are included in the study are required to sign an informed consent form and will participate in the study on a voluntary basis. The researchers will obtain written informed consent from each participant before screening. The informed consent form (in Chinese) is provided in Supplemental file 2. The schedule of patient enrolment, intervention, and assessment is illustrated in Fig. 2.

**Fig. 2 Fig2:**
[figure not shown]
Schedule of enrolment, interventions, and assessments according to the Standard Protocol Items: Recommendations for Interventional Trials (SPIRIT) guidelines. D, day; T, time; Tre, treatment; JTN, Jin’s three-needle acupuncture; MT, mirror therapy; FMA-UE, Fugl–Meyer Assessment for Upper Extremity; MAS, motor assessment scale; ARAT, the action research arm test; ADL, activities of daily living; fMRI, functional magnetic resonance imaging; RT, routine test

### Participants

#### Recruitment procedures

Researchers of the study will recruit 60 eligible patients with upper limb motor dysfunction after CIS from Shenzhen Hospital of Guangzhou University of Traditional Chinese Medicine (Futian). Eligible patients must meet the inclusion and exclusion criteria. Information about this trial will be available through posters, and leaflets will be distributed to inpatients and outpatients at multiple locations in the hospital. Interested patients can contact the project leader through their therapists, among others, by telephone and email. If an applicant meets the study criteria, they will be invited to participate. The following basic personal information will be collected: sex, age, body mass index (BMI), educational background, occupation, marital status, related past health history, etc. These details about the participants will be maintained by the data monitoring committee (DMC) and will never be revealed to any individual or organization not connected to the study.

#### Randomization

A total of 60 participants who meet the inclusion criteria will be randomly allocated into the combined treatment group (JTN+MT) and JTN group. A statistician blinded to the treatment and data collection will use Strategic Applications Software (SAS, version 9.1.3, SAS Institute Inc., Cary, NC, USA) to generate the random allocation sequence. The group name will be written on a card and sealed in an opaque envelope. The sequence numbers will be written on the envelopes, and the envelopes will be numbered sequentially. Random allocation will be performed for participants who meet all selection standards and signed the Consent Form. The research coordinator will allot participant identification codes and record the codes in the Case Report Forms. The therapists will open random allocation envelopes sequentially and allocate the participants accordingly. The details (such as name, sex, age, and date of inclusion) of newly included participants will be recorded before randomization. The opened envelopes will be separately stored in lockers.

#### Blinding

Because of the characteristics of therapy, the acupuncturists in this study cannot be blinded to the assignment while the participants cannot be blinded to the MT, but the outcome assessors, data manager, and statistics analyzer will evaluate the results of the study without being aware of subject allocation. The evaluators of the final intervention effect are blinded that can effectively avoid the bias caused by subjective factors in the evaluation. The blinding will be monitored and assessed by independent statisticians responsible for data monitoring and by the Ethics Committee of the study center. The blind code will be disclosed after completion of the statistical analysis.

### Intervention

Both treatments will be conducted for six consecutive days per week and last for 4 weeks. We will use No. 30 disposable acupuncture needles (size 0.32 mm × 25 mm or 0.32 mm × 50 mm stainless steel disposable acupuncture needles (Suzhou Huatuo Medical Instrument Factory) for the intervention. The quality of the needles will be checked before conducting the treatment to ensure safety.

The practitioners of this trial have more than 5 years of clinical experience and have participated in a training session to ensure that the treatments will be administered consistently. The patient may make an appointment with the physician before starting the treatment, and confirmation will be made by a phone call to enhance compliance.

#### JTN combined with MT group

This study uses the method of staged acupuncture [22]. According to Jin’s three-needle theory combined with previous related research [23], every point group is compatible with some kind of disease or a series of symptoms. Thus, in the soft paralysis period, temporal three needles [temporal I needle: 2 cun (a unit of length (=1/3 decimeter)) on the tip of the ear; temporal II and temporal III needle: 1 cun in front of and behind the temporal I needle] and hand three needles [LI11, TE5, LI4] will be used at the main point. In the spasm phase, temporal three needles and clonic three needles of the upper limbs [PC6, HT1, LU5] will be taken as the main point. Wisdom three needles [GV24, GB13] will be used with syndrome differentiation.

“Scalp-cortex theory” [24] has indicated that the effective rate of temporal acupuncture for stroke patients was 97%, among which 67.6% patients had significantly improved upper limb muscle strength. It has been reported [7] that hand three needles and clonic three needles of the upper limbs will coordinate and balance the muscle tension between agonistic muscles and antagonistic muscles, promote the transformation of joint movement to separate movement, and relieve upper limb tightness, paralysis, pain, sensory disturbance, and so on. The combined effect of these acupoints will promote the recovery of upper limb function.

Participants will be treated by therapists with more than 5 years of clinical experience. Patients will be in the supine position. Acupoints will be sterilized with alcohol, and the target position will then be fixed by the therapist’s left hand. The therapist’s right hand will insert thin, disposable acupuncture needles.

Among the selected points, LI11, TE5, LI4, PC6, HT1, and LU5 will be needled unilaterally based on the affected side of the patient. HT1 will be needled at 45°–90° to the body surface and inserted to a depth of 0.3–0.5 cun. TE5, LI4, and PC6 will be needled at 90° to the body surface and inserted to a depth of 0.5–1.0 cun. LI11 and LU5 will be needled at 90° to the body surface and inserted to a depth of 1.0–1.5 cun. Temporal three needles will be needled at 15°–30° to the body surface and inserted to a depth of 0.3–0.5 cun. Following insertion, stimulation of the acupuncture point will be performed with bidirectional rotation of the needle sleeve at approximately 18–300 per min. The acupuncture manipulation will be adjusted according to the tolerance of each patient with the methods of tonifying and purging to achieve the feeling of “deqi” without obvious pain. The needles will be maintained in place for 30 min. A sterilized, dry cotton ball will be gently pressed against the point to prevent bleeding when each needle is withdrawn. The entire course of treatment will occur over 30 min, while the upper limbs will be treated with MT.

During MT, patients who pass the kinesthetic and visual imagery questionnaire (KVIQ) test will sit close to the table. A 5 cm × 35 cm mirror will be placed vertically between the upper limbs on the table, with the reflecting surface facing the uninjured limb. Patients will be asked to observe the motion of the upper limb on the uninjured side and imagine that the limb on the affected side was in motion, imagine the motion of the affected limb the same as that observed on the uninjured side, and complete 6 movements including shoulder joint forward flexion, elbow joint flexion and extension, forearm forward and backward rotation, wrist joint flexion and extension, finger extension and grasping, and thumb abduction. The participants will be asked to perform each movement for 5 min and try to reach the maximum range of motion of the joints. Training will be completed for 30 min per day.

For the period of treatment, acupuncture and mirror training were performed 6 times per week for 4 weeks.

#### JTN group

In the control group, the acupuncture therapy will be the same as the treatment group’s.

#### Concomitant treatments

The patients in two groups will be treated with basic medications in the meantime. The patients in two groups will be treated with basic medications according to guidelines for clinical management of cerebrovascular disorders [25] to control blood pressure: individual treatment is adopted to stabilize blood pressure below 135/85 mmHg or within the normal range, control blood sugar and lipid, and prevent platelet aggregation.

The patients in the two groups will be provided with instructions to discourage them from receiving any additional specific complementary treatments related to upper limb dysfunction after CI throughout the trial, including abdominal acupuncture, fire acupuncture, floating acupuncture, and other acupuncture therapies, moxibustion, herbal medicine, massage, etc. If a patient needs other prescription medication, the relevant information will be recorded in the Case Report Form for that patient. The data will be assessed by two blinded researchers, to ensure whether be included.

For follow-up, all participants will participate in a 12-week follow-up after 4 weeks intervention. At the end of a 12-week follow-up period, participants will be referred for clinical evaluation to assess their functional status, including Fugl–Meyer Assessment for Upper Extremity (FMA-UE), motor assessment scale (MAS), action research arm test (ARAT), and activities of daily living (ADL) scale.

### Outcome measures

The study period is 16 weeks. FMA-UE, MAS, ARAT, ADL, and fMRI will be assessed before and after the treatment, as well as safety indicators such as blood routine test, urine routine test, stool routine test, liver and kidney function examination, and blood glucose. All the patients will take FMA-UE, MAS, ARAT, and ADL assesses after 12 weeks follow-up. Health economic indicators were recorded at week 4 and week 16. All outcomes will be measured by several experienced assessors who are blinded to the randomization group after the baseline visit for evaluation. All assessors will be trained to administer these assessments.

#### Primary outcomes

The primary outcomes in this study are the mean change in the scores on the FMA-UE from baseline to 4 weeks intervention and 12 weeks follow-up, as well as fMRI between the two groups and within groups from baseline to 4 weeks intervention.

FMA-UE is widely used for motor function assessment and can reflect the functional level of stroke subjects. The upper extremity has a maximum score of 66 points divided into three parts, namely shoulder arm (36 points), wrist hand (24 points), and coordination (6 points) and higher score indicate better upper limb movement function [4]. The FMA-UE is the most common scale for evaluating upper limb motor function after CIS. It is often used as a gold standard for testing the validity of other scales as well [26, 27]. The FMA-UE has excellent reliability and validity and is sensitive enough for clinical and research practice [28].

fMRI is a noninterventional imaging technique that uses magnetic resonance to measure changes in brain hemodynamics caused by neuronal activity as a reflection of the activation state of brain areas. For the observation methods, after the patients are ready, scanning will be performed on the whole brain of the patients. During resting-state scanning, patients will be instructed to relax, close their eyes, and avoid systematic thinking activities as much as possible. After resting-state scanning for 6 min, functional state scanning will be performed. The experimental task will be designed in blocks. There will be 10 trials for each task state (Fig. 3), and the time of each trial is 30 s. In addition, there are 10-s empty sweeps before each scan, so each scan is 5 min and 10 s. Once in place, the subjects will be put on noise-canceling earphones and receive instructions. Patients will be asked to try to imagine their fingers flexing when they hear the word “close.” When they hear the word “open,” they will be asked to try to imagine their fingers straightening. Each subject will receive task training in advance.

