### Sample size

The sample size was calculated based on the effective rate of the treatment. Based on similar previous studies [30], we assumed the effective rate of 88.9% and 56.1% in the JTN+MT group and the control group, respectively. The PASS11.0 software was used to perform a power analysis to determine the sample size. Type-1 error was assumed at 0.05, type-2 error at 0.2. The required sample size was 26 subjects for each group. Considering a dropout rate of 15%, a total of 60 subjects needed to be enrolled (30 participants per group).

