### Data collection and statistical analysis

Therapists will collect the data using Case Report Forms. Two independent researchers will then input the data into the database. All analyses will be carried out under the guidance of independent data monitors to ensure the security and dependability of the data. About the dropped-out participants, their number and the reason for termination will be recorded, especially for adverse events. All enrolled patients will be included in the primary analysis conducted in accordance with the intention-to-treat (ITT) principle. The data will be analyzed by SPSS for Windows version 19.0. The statistical significance is defined as a two-sided *P* value of ≤ 0.05. The baseline characteristics will be reported as the means ± standard deviation (SD). For comparison of baseline materials, a chi-squared or Fisher’s exact test will be used for categorical variables, Student’s *t* test will be used for normally distributed data, and the Mann-Whitney *U* test will be used for non-normally distributed data. The scores of each rating scale and laboratory index before the intervention will be compared between the groups via Student’s *t* test or the Mann-Whitney *U* test. For the comparison within groups, the changes in the scores and indexes from baseline to endpoint will be assessed by a paired *t* test or the Wilcoxon rank-sum test. For the difference between groups, we will use Student’s *t* test or the Mann-Whitney *U* test. For the safety analysis, the adverse events will be listed and analyzed using a chi-squared or Fisher’s exact test. For participants who discontinue or deviate from intervention, listwise deletion or multiple imputation will be used.

The data of fMRI will be analyzed by professional technicians at the Shenzhen Advanced Institute.

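### The primary outcome is not settled: FMA-UE at two times and fMRI between and within groups are all primary at one undivided 0.05, while the abstract names a single, different primary

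*Protocol article*

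**What the plan says.** Four places in the protocol article bear on this.

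- **Outcome measures, Primary outcomes.** The section uses the plural. It makes FMA-UE mean change primary at two times, the end of treatment and the end of follow-up, and the same sentence then adds imaging: "as well as fMRI between the two groups and within groups from baseline to 4 weeks intervention". The effective rate is not in this list.
- **Abstract, Methods/design.** A single primary outcome is named, the effective rate based on the FMA-UE. The other outcome measures end with "activities of daily living (ADL) scale, and fMRI analyses".
- **Sample size.** The calculation uses the effective rate: "we assumed the effective rate of 88.9% and 56.1% in the JTN+MT group and the control group, respectively". The error rates are given once: "Type-1 error was assumed at 0.05, type-2 error at 0.2".
- **Data collection and statistical analysis.** One threshold is set for the trial: "The statistical significance is defined as a two-sided" P value of at most 0.05. Between-group differences use a t test or Mann-Whitney test, and within-group changes use a paired test. fMRI has only a closing sentence, which gives the analysis to technicians at another institute and states no threshold.

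The article does not rank the primary outcomes, divide alpha among them or require that all of them succeed.

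**The concern.** Which outcome decides the trial is a matter for the protocol, and this article gives two answers. Under the abstract, the trial turns on a responder proportion, and fMRI is supportive. Under the outcomes section, it turns on two FMA-UE mean changes and on fMRI, and the responder proportion is absent.

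Two separate things are at stake. The first is error control. With several unranked primaries and a single 0.05, a report could present whichever one is significant as the primary result. The second is the kind of evidence. A change from baseline inside one arm is given primary status, although the stated question (Discussion) is whether the combination is more effective than the single method. Only a comparison between the arms answers that.

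**Working it through.** **1. The plan's own figure.** Inputs (Sample size section): 88.9% against 56.1%, alpha 0.05, power 0.80. With the two-sided unpooled normal formula:

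n = (1.96 + 0.8416)² × [0.889 × 0.111 + 0.561 × 0.439] / (0.889 − 0.561)² = 7.849 × 0.34496 / 0.10758 = 25.2, so 26 per group.

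This agrees with "The required sample size was 26 subjects for each group". The pooled formula gives 28. Multiplying 26 by 1.15 gives 29.9, so 30 per group, as in "Considering a dropout rate of 15%, a total of 60 subjects needed to be enrolled (30 participants per group". The arithmetic reproduces, but for one test of the effective rate at an undivided 0.05. It says nothing about power for FMA-UE mean change or for fMRI.

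**2. Two FMA-UE times.** Each test is at two-sided 0.05, there is no true effect, and success at either time is taken to be enough. The quantity is P(|Z₁| > 1.96 or |Z₂| > 1.96) for two correlated normal statistics. The article gives no correlation, so a range is assumed.

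| Assumed correlation | Two FMA-UE tests | Plus one independent fMRI test |
|---|---|---|
| 0.5 | 9.1% | 13.6% |
| 0.7 | 8.3% | 12.9% |
| 0.9 | 7.0% | 11.7% |

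**3. Adding one between-group fMRI test.** The last column is 1 − (1 − two-test rate) × 0.95; for correlation 0.5, 1 − 0.909 × 0.95 = 0.136. It assumes that fMRI is reduced to one measure, is judged at 0.05 and is independent of FMA-UE. If fMRI correlates 0.3 with both FMA-UE tests, simulation gives 13.3% down to 11.4% over the same range. More fMRI measures or regions at 0.05 would raise the rate.

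**4. Within-group fMRI change.** This is not a test of the treatment difference, so it is kept out of steps 2 and 3. Suppose both arms change equally, so that mirror therapy adds nothing, with 30 patients per arm and a paired t test at 0.05. For an assumed standardised change of 0.3, one arm is significant with probability 0.355, and at least one of the two with probability 1 − 0.645² = 0.58. For 0.5, the figures are 0.754 and 1 − 0.246² = 0.94. The sizes of change are assumptions, but the article gives reasons to expect some change in both arms. Patients enter 2 weeks to 6 months after stroke (Inclusion criteria), both arms receive the same acupuncture (JTN group) and both receive basic medication (Concomitant treatments).

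**5. Cost of dividing alpha.** As an illustration on the effective rates, Bonferroni over three between-group tests gives 0.05 / 3 = 0.0167 each. By the pooled formula, 38 per arm are then needed before dropout, against 28 at 0.05, and power at 30 per arm is about 69%. A single primary with a fixed sequence keeps 0.05 and needs no division of alpha.

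**The case against.** The strongest reply is that this is a condensed article. Handling of multiplicity and the exact fMRI contrast are commonly left to an analysis plan, and an unseen plan may deal with both. That stands as far as it goes: the lack of an adjustment method, or of a named brain region, is not a finding here. It does not remove the conflict. The abstract and the outcomes section disagree on what is primary, and an analysis plan would have to choose between them.

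A second reply is that the 0.05 sentence follows the mention of SPSS and precedes the tests for rating scales, laboratory indexes and adverse events, so it may not govern fMRI at all. This also stands. Only the FMA-UE tests clearly fall under it, so the 12% to 14% is conditional.

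A third is that no any-one-suffices rule is written, and that efficacy and mechanism are presented as separate aims. This is fair. The inflation depends on that reading, and if every primary had to succeed there would be none. But no such requirement is written, and the Discussion calls the fMRI results a reference for evaluating clinical efficacy, so the separation is not clean.

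A reader might go further and count five tests (two FMA-UE, one between-group fMRI, two within-group fMRI), giving 1 − 0.95⁵ = 22.6%. The documents do not support that figure. The between-group fMRI contrast is the difference of the two within-group changes, so the tests are not independent; with that link and an FMA-UE correlation of 0.7 it would be 18.9%. More fundamentally, within-group tests do not address the treatment difference. Giving each a 5% chance of a positive result also contradicts the expectation that both arms will change.

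**Conclusion.** The concern holds in a limited form. The article fixes several unranked primaries at one undivided 0.05 and contradicts its own abstract on both the FMA-UE measure and the status of fMRI. If either FMA-UE time suffices, the false-positive rate is about 7% to 9% instead of 5%. It is about 12% to 14% if one between-group fMRI test is added at an assumed 0.05. The correlations, the any-one rule and the fMRI threshold are assumptions, and the article supplies none of them.

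Primary status for within-group fMRI change is a fault of inference and does not belong in a family-wise error rate: such a change can be significant in either arm with no benefit from mirror therapy. The stated sample size reproduces, so the fault lies in the choice and ordering of endpoints.

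**What to change.** Make a dated amendment before unblinding that does the following:

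1. Declares one primary: the between-group FMA-UE comparison at week 4, at two-sided 0.05. It must say whether this is the effective rate (abstract, Sample size) or the mean change (Primary outcomes).
2. If it is the mean change, restates the power on that measure, because the present calculation covers only the effective rate.
3. Tests FMA-UE at the 12-week follow-up (week 16) only if the primary is significant.
4. Moves fMRI to secondary or mechanistic, with inference only on the between-group difference in change.
5. Reports within-group changes descriptively.
6. Brings the abstract, the outcomes section and the sample size section into agreement.

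The hierarchy itself adds no patients. fMRI and follow-up FMA-UE lose stand-alone primary status. This is more than a wording change: recruitment was planned from January 2018 to the end of December 2020, and the Ethics and dissemination section requires modifications to be reported to the ethics committee and the registry. The power check under item 2 may show less than 80% for the mean change, and that should be stated openly if so.
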